#### Physical activity level

Changes in physical activity level will be measured using the Active Australia Survey (AAS).^75^ The AAS is a validated self-report tool containing eight core questions to assess participation (hours/min per week) in moderate and vigorous-intensity physical activity and walking for recreation, over the previous week.

#### Sleep hygiene behaviours

Changes in sleep hygiene behaviours will be measured using the Pittsburgh Sleep Quality Index (PSQI).^76^ The PSQI is a validated self-report survey with 19 self-rated items and 5 items rated by the bed partner or roommate (if applicable). The tool assesses seven components of sleep to provide one global score. Components measured include (1) subjective sleep quality, (2) sleep latency, (3) sleep duration, (4) habitual sleep, (5) sleep disturbances, (6) use of sleeping medication and (7) daytime dysfunction. The overall global score of sleep quality will be calculated and the subcomponents reported.

#### Healthcare utilisation

For the purpose of conducting a cost analysis, the Consumer Services Receipt Inventory (CSRI)^77^ will be completed by participants at each time point. The CSRI is an adaptable tool that ensures the format, language, scope and content are compatible with the research aims, context, participants’ likely circumstances, and the quantity and precision of information required.^78^ Healthcare utilisation is captured through self-report and includes information on the number of appointments and type of healthcare services used in the preceding 3 months.

#### Cost analysis

A cost–consequence analysis will be conducted including calculating the cost of each intervention (ie, active, passive and control) and reporting intervention costs alongside mean change outcomes. Intervention costs will be recorded in terms of cost of intervention development, intervention delivery and the operating costs of the randomised controlled trial. Outcomes to be reported as part of the cost analysis will include mean change in addictive eating symptom scores assessed using the YFAS (ie, the primary outcome), as well as mean change in the number of healthcare appointments in the past 3 months assessed using the CSRI, and mean change in quality-adjusted life years assessed using the EQ-5D-5L. This approach was selected to provide a comprehensive and transparent overview of intervention costs, given the lack of cost analysis data in this area of research.^79 80^

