## Methods

### Study trial design

The TRACE Programme is a randomised controlled trial with three parallel arms. Assessments will be carried out at three time points: (1) baseline (pre-intervention), (2) 3-month post-baseline (primary time point) and (3) 6-month post-baseline follow-up assessment. This project was approved by the University of Newcastle Human Research Ethics Committee (H-2021-0100) and prospectively registered with the Australian New Zealand Clinical Trials Registry (ACTRN12621001079831). The study protocol was developed in accordance with the Standard Protocol Items: Recommendations for Interventional Trials (SPIRIT) guidelines.^51^ The design, conduct and reporting of the studies will adhere to the CONSORT (Consolidated Standards of Reporting Trials) guidelines.^52^ All participants will provide informed electronic consent (see online supplemental material 1 for a copy of the consent form) to participate and can withdraw at any time for any reason. The funding bodies had no role in the design, conduct or reporting of the study.

10.1136/bmjopen-2022-064151.supp1Supplementary data

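### Healthcare use is defined as a change in a 3-month appointment count, with no time point, 6-month total or service type named, although the planned survey supplies all three

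*Protocol article*

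**What the plan says.** The Cost analysis section of the protocol article plans a cost–consequence analysis that sets the cost of each arm beside mean changes in outcomes. Its list opens with "Outcomes to be reported as part of the cost analysis will include mean change in addictive eating symptom scores" and goes on to the healthcare-use item, "mean change in the number of healthcare appointments in the past 3 months assessed using the CSRI". On the cost side it states: "Intervention costs will be recorded in terms of cost of intervention development, intervention delivery and the operating costs of the randomised controlled trial". The reason given for the approach is: "This approach was selected to provide a comprehensive and transparent overview of intervention costs".

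The Healthcare utilisation section says that the CSRI is collected for the cost analysis, that it "will be completed by participants at each time point", and that it "includes information on the number of appointments and type of healthcare services used in the preceding 3 months". Table 1 ticks it at baseline, 3 months and 6 months, and the Study trial design section gives the same three assessments.

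For healthcare use, the Cost analysis section therefore fixes the measure (a count of appointments), the window (the past 3 months) and the form (mean change). It does not fix the time point, and it mentions neither a 6-month total nor service type.

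**The concern.** Healthcare use accumulates. The natural figure to set beside the cost of delivering an arm is how much care its participants used during follow-up. A change score instead takes one follow-up window and subtracts a window from before the trial.

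Two things are at stake:

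- **Coverage.** The wording permits a single change, to 3 months or to 6 months, and either would leave out the other half of follow-up. A shift in use confined to the omitted half would not be seen.
- **Precision.** Subtracting a noisy pre-trial count in full adds variance that adjustment for the same count would avoid.

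A third, smaller matter is content. Read plainly, the number of appointments is one count across unlike services. A rise or fall in that count does not tell the reader which services changed.

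**Working it through.** The plan states no figure for this outcome, so there is none to reproduce. The check has two parts.

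**1. Which months are covered**

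Inputs: 3-month recall (Healthcare utilisation); follow-up surveys at 3 and 6 months (Study trial design, Table 1).

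- 3-month survey alone: months 1–3, which is 3/6 = 50% of follow-up.
- 6-month survey alone: months 4–6, which is 3/6 = 50%.
- Both surveys: months 1–6, which is 6/6 = 100%, with no gap or overlap.

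Total use over follow-up is therefore the 3-month count plus the 6-month count. An illustration with assumed mean counts:

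| Baseline | Months 0–3 | Months 3–6 | Change at 3 months | Change at 6 months | Total, months 0–6 |
|---|---|---|---|---|---|
| 4 | 6 | 4 | +2 | 0 | 10 |
| 4 | 4 | 6 | 0 | +2 | 10 |

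The two patterns have the same total. A single change reports +2 for one and 0 for the other. The two changes together recover the total: their sum is +2, which equals 10 − 2 × 4.

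**2. Precision when both windows are used**

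Assumptions, none of them from the document: each 3-month count has variance s², any two windows have correlation r, and the arm effect is the same in each window. Let M be the mean of the two follow-up counts and B the baseline count. The total is 2M, so relative precision is the same for M and for the total.

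- Var(M) = s²(1 + r)/2, and Cov(M, B) = r s².
- Average of the two changes, M − B: s²[(1 + r)/2 + 1 − 2r] = 1.5(1 − r)s².
- M adjusted for B by regression (slope r): s²[(1 + r)/2 − r²].

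| Assumed r | Average change (× s²) | Baseline-adjusted (× s²) | Variance ratio | Interval-width ratio | Narrower by |
|---|---|---|---|---|---|
| 0.3 | 1.05 | 0.56 | 0.533 | 0.730 | 27% |
| 0.5 | 0.75 | 0.50 | 0.667 | 0.816 | 18% |
| 0.7 | 0.45 | 0.36 | 0.800 | 0.894 | 11% |

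Both quantities use the same two windows and, under randomisation, estimate the same difference between arms. The gain comes only from adjusting for baseline instead of subtracting it.

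**The case against.** The strongest reply is that the article discards nothing in so many words. It names no time point, and the CSRI is collected at all of them. If changes at both 3 and 6 months are reported, coverage is complete and the total can be recovered. The outcome list is introduced by a phrase that leaves it open, and a table by service type is not excluded. A condensed article may leave such detail to a fuller plan. A cost–consequence analysis may also report consequences in natural units, and the section plans no test or interval for appointments, so no stated precision goal is harmed.

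Most of this stands. A reader might infer that half of the 6-month use and all information on service type will be thrown away. The document does not say so: the first follows only if a single time point is used, and the second only if counts are pooled and no breakdown is shown. A reader might also compare a single-window change, with variance 2(1 − r)s², with the adjusted two-window mean and quote intervals 37%, 29% and 23% narrower. That sets the least favourable reading of the plan against the best alternative and should not be used as the size of the problem. Nor can it be said that costs and consequences must cover different periods. The five sessions run in weeks 1–12 and the passive workbook is meant to be finished within 3 months, so a change to 3 months would span the main delivery period.

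The reply does not remove the choice of form. Mean change in a past-3-month count is a stated method, not a gap left for another document. On the generous reading, with both windows reported, it is still less precise than the adjusted total.

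**Conclusion.** The point holds as a minor improvement to a secondary economic outcome. The article defines healthcare use as a change from a pre-trial window in a 3-month count, without a time point, a total over follow-up or a service type, although the planned data support all three.

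If one time point is used, 50% of follow-up is missed. This is a risk that the wording leaves open, not a stated loss. If both are used, the cost is precision alone: the adjusted total gives intervals about 27%, 18% and 11% narrower at r = 0.3, 0.5 and 0.7. Those figures rest on assumed correlations, equal variances and a common correlation across windows, with a constant arm effect per window. No value of r can be taken from the document.

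The lack of a valuation of healthcare use at unit cost is a matter of scope and is not part of this finding.

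**What to change.** In the Cost analysis section, define the healthcare-use consequence as total appointments over months 0–6, that is, the 3-month report plus the 6-month report. Compare arms with the baseline count as covariate, and show the total by service type.

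Where one follow-up report is missing, fit a mixed model to the 3- and 6-month counts with the baseline count as covariate, and take the sum of the two time-point contrasts between arms. A participant with one report then still contributes. Baseline should enter as a covariate here: the model in the Statistical analysis plan section treats baseline as one of the repeated responses, and with complete data its group-by-time contrast equals the unadjusted difference in change.

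The cost is a change of wording and a slightly longer table. The data are already planned. Unit costing may be added if wanted, but it is optional.

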### Mediators/moderators

The following potential mediators and moderators of intervention efficacy will be examined:

#### Trait/s associated with personality and risk of addictive behaviour

Participants will complete the Substance Use Risk Profile Scale (SURPS)^81^ at baseline to determine their dominant trait/s. The SURPS is a validated self-report 23-item survey that assesses four traits associated with increased risk of addictive behaviours (impulsivity proneness, sensation proneness, depression proneness and anxiety proneness).

#### Eating behaviours

Eating behaviours that have been shown to have overlap with addictive eating will be measured. This includes eating disorders, binge eating, grazing behaviours and reward-driven eating. Eating disorders will be measured using the Eating Disorder Examination Questionnaire 6.0 (EDEQ-6.0)^62^ The EDEQ-6.0 is a validated self-report 28-item questionnaire that assesses the occurrence and frequencies of key eating disorder behaviours with cognitive subscales related to eating disorders (restraint, eating concern, shape concern and weight concern) and behavioural symptoms related to these concerns (eg, frequency of binge eating, vomiting, use of laxatives or diuretics, and overexercise). Subscale and global scores reflect the severity of eating disorder psychopathology. Binge eating will be measured using the Binge Eating Scale (BES).^82^ The BES is a validated self-report 16-item questionnaire to assess the presence of certain binge eating behaviours, over the past 28 days, which may be indicative of an eating disorder. Each item contains three to four statements about behaviours, thoughts and emotional states. Grazing behaviours will be measured using the Short Inventory of Grazing (SIG).^83^ The SIG is a validated self-report two-item measure to assess (1) the presence and frequency of grazing in general, and (2) the presence and frequency of grazing accompanied by a sense of loss of control. Reward-driven eating will be measured using the Reward-Based Eating Drive Scale (REDX-5).^84^ The REDX-5 is a validated self-report five-item questionnaire, in a 5-point Likert scale format from 1 (strongly disagree) to 5 (strongly agree), that assesses reward-driven eating (loss of control over eating, lack of satiety and preoccupation with food).

#### Participant activation level

Participants’ underlying knowledge, skills and confidence in managing their addictive eating behaviours and overall health will be measured using the Patient Activation Measure (PAM-13).^85^ The PAM-13 is a validated self-report 13-item scale that draws on concepts such as health locus of control, self-efficacy in managing health behaviours and readiness to change health behaviours.^64 86^ Higher PAM-13 scores indicate that individuals have higher levels of activation, and understand their role in the self-management process and feel capable of fulfilling that role.^87^ Research has demonstrated that a single-point change in PAM score is meaningful.^88^

### Engagement and use of the programme website and Facebook group

Interaction with the website will be objectively tracked throughout the study (baseline to 6 months, that is, time points 1–3) using Google Analytics (Google). Measures of engagement and usage will include number of website visits, website visit duration, number of page views and links accessed/resources downloaded.

Interaction with the Facebook group will be measured throughout the post-intervention period (3–6 months from baseline, that is, time points 2–3). Measures of engagement and usage will include number of participants to join the Facebook group, and number of views, likes and comments per post.

### Study sample characteristics

Sociodemographic data will be collected by an online questionnaire at baseline. Participants will provide information on their age, sex, marital status, postal code, years of education, employment status and current living situation. Index of Relative Socio-Economic Disadvantage score,^89^ based on the Australian Bureau of Statistics census data and reflecting a proxy index of socioeconomic status, will be determined by postal code of residence. Current smoking and substance use will be measured using the Alcohol, Smoking and Substance Involvement Screening Test V.3.0.^59^ Additionally, previous treatment sought for overeating from health professionals or products used to treat overeating will be collected.

Anthropometric data (self-reported height and weight) will be collected by online questionnaire at baseline. BMI will be calculated using standardised techniques and categorised according to the WHO adult cut-off points.^90^

### Sample size

The sample size for the study was calculated based on data from the feasibility study,^24^ given the absence of other intervention studies. Through guidance with statisticians, a large effect size was chosen and needed to enable the possibility of a clinically meaningful result. A clinically meaningful difference in symptoms of addictive eating was selected as a decrease of two symptoms, given this would correspond to a change in severity classification on the YFAS 2.0 tool. To detect a mean two-unit difference (SD=2.2) in the YFAS symptoms between the active intervention group and the passive intervention group or control group and using a standardised effect size of d=0.91, a sample size of 32 individuals per group (total sample size n=96) is required to detect this change with a power of 0.90 and a type 1 error rate set at 0.025 to account for multiple testing. However, allowing for a 30% dropout rate from the pilot, a sample size of 46 individuals per group (total sample size n=138) would be required. Therefore, a total sample size of 150 individuals, with 50 per group, was chosen to remain conservative.

### Statistical analysis plan

Data analysis will be conducted by a researcher blinded to the intervention conditions. Descriptive statistics of sample characteristics will be presented. For the primary YFAS outcome, a linear mixed model (LMM) will be based on a model with main effects for group (active intervention, passive intervention, control) and time (treated as categorical at levels baseline, 3 and 6 months), and the group-by-time interaction. An unstructured residual covariance structure will be used to allow for correlation between the repeated measurements for a subject. The primary outcome effect will be reported as the difference between means at baseline and 3 months, with a 95% CI for the difference. Mental health condition and BMI will be examined for possible moderating effects on the effect size, and if so, adjustment for them will be carried out. Secondary descriptive analysis will be carried out to identify whether specific symptoms were predominantly associated with reductions in YFAS score.

A secondary outcome will be a categorical variable, clinically significant change from baseline to 3 months, where significant requires a reduction of two or more symptoms in the YFAS. This will be analysed using logistic regression with group being the only factor. Additional secondary outcomes will include dietary outcomes (average daily energy intake, proportion of total energy intake contributed by core food and non-core food intake, macronutrient intake, micronutrient intake and overall diet quality) and mental health status (depression, anxiety and stress scores). These will also be analysed using LMMs as per the approach above. All available data will be used with no imputation of missing values at 3 and 6 months; however, baseline scores will be kept. The participants will be analysed according to their allocated randomisation group consistent with an intention-to-treat analysis. Statistical significance will be set at 0.05.

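### The primary mixed model leaves each arm's baseline YFAS mean free, so its treatment contrast is a difference in change: valid, but less precise than a common-baseline model using the same data

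*Protocol article*

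**What the plan says.** The Statistical analysis plan section of the protocol article describes the primary linear mixed model as "a model with main effects for group (active intervention, passive intervention, control) and time (treated as categorical at levels baseline, 3 and 6 months". The interaction of group with time is included as well. On covariance it states: "An unstructured residual covariance structure will be used to allow for correlation between the repeated measurements for a subject". The reported effect is described thus: "The primary outcome effect will be reported as the difference between means at baseline and 3 months, with a 95% CI for the difference".

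Baseline YFAS is not named as a covariate, and no constraint on the baseline means is stated. The only adjustment mentioned is for mental health condition and BMI, and it is made only if these turn out to moderate the effect. The same model is to be used for the dietary, depression, anxiety and stress outcomes. All available data are used, without imputation, and baseline scores of participants lost to follow-up are retained.

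Table 1 places the only pre-randomisation YFAS at eligibility screening. The Study procedure section puts allocation after completion of the baseline surveys. Under Randomisation and blinding, stratification is by sex and mental health status, not by YFAS.

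The Sample size section sets the target as follows: "To detect a mean two-unit difference (SD=2.2) in the YFAS symptoms between the active intervention group and the passive intervention group or control group". The standardised effect that goes with it is 0.91. The section asks for 32 per group at power 0.90 and type 1 error 0.025, rising to 46 for 30% dropout, with 50 per group chosen.

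**The concern.** Three arms by three times with a full interaction gives nine free means, three of them at baseline. Because YFAS is taken before allocation, any baseline difference between arms is chance. The model nevertheless estimates that difference and subtracts all of it from the 3-month difference. With equal SDs at the two times, only a fraction rho of a chance baseline difference is expected to persist to 3 months. Subtracting the whole of it adds noise.

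What is at stake is precision on the primary outcome and on every secondary outcome analysed the same way, in a trial of 50 per arm that expects 30% dropout. The article reports recruitment as completed, so the analysis is the main remaining place to gain precision.

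**Working it through.** **Inputs.** From Sample size: difference 2, SD 2.2, 32 per group, power 0.90, alpha 0.025, dropout 30%, 50 enrolled per group. From Statistical analysis plan: the model above, with all baselines kept. Assumed, because the article does not give them: the correlation rho between baseline and 3-month YFAS, shown over a range, and equal SDs at the two times. The reported effect does not name a between-arm contrast; I read it as the 3-month group-by-time contrast.

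**1. The plan's own figure.** A two-sample t-test with difference 2, SD 2.2 and two-sided alpha 0.025 has power 0.897 at 31 per group and 0.907 at 32. So 32 is reproduced. 32/0.70 = 45.7, hence 46. 50 × 0.70 = 35 expected completers per arm. The calculation contains no baseline-to-follow-up correlation.

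**2. What the planned contrast is.** On simulated complete data, generalised least squares with nine free means and unstructured covariance gave a 3-month interaction contrast of -2.6676. The plain difference in mean change was also -2.6676.

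**3. Variance per arm, in units of SD².** Let n be the participants with 3-month data and N those with a baseline.

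- Planned model: (1-rho²)/n + (1-rho)²/N
- Common-baseline model: (1-rho²)/n

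The second term comes from estimating a separate baseline mean in each arm. With one common mean it cancels from the between-arm difference. With complete data (N = n) the planned variance becomes 2(1-rho)/n, and the ratio of common-baseline to planned is (1-rho²)/[2(1-rho)] = (1+rho)/2.

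**4. Ratios.** SD cancels, so these do not depend on what 2.2 means.

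| rho | Complete data, (1+rho)/2 | First term, (1-rho²)/35 | Second term, (1-rho)²/50 | Ratio with n=35, N=50 |
|---|---|---|---|---|
| 0.3 | 0.65 | 0.0260 | 0.0098 | 0.0260/0.0358 = 0.73 |
| 0.5 | 0.75 | 0.0214 | 0.0050 | 0.0214/0.0264 = 0.81 |
| 0.7 | 0.85 | 0.0146 | 0.0018 | 0.0146/0.0164 = 0.89 |

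At rho 0.5 in the trial as enrolled, 1/0.811 = 1.23, so the gain equals about 23% more participants at the same dropout.

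**5. Power, only if 2.2 is the SD of scores at a single time** (difference 2, two-sided alpha 0.025).

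| rho | Planned, 32 complete pairs per arm | Planned, 50 baselines and 35 follow-ups per arm | Common baseline, 35 follow-ups per arm |
|---|---|---|---|
| 0.3 | 78% | 86% | 95% |
| 0.4 | 84% | 91% | 97% |
| 0.5 | 91% | 95% | 98% |

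Under this reading the planned contrast reaches 90% power at rho of about 0.49 with 32 complete pairs, and about 0.38 in the trial as enrolled. If 2.2 is instead the SD of change, the power at 32 per arm is 0.907 whatever rho is.

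**The case against.** The strongest reply is that group, time and their interaction with unstructured covariance is a standard analysis. It is unbiased under randomisation, and the section contradicts nothing in specifying it. That stands: this is a loss of precision, not an error of validity.

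A reader might infer that the trial misses its 90% power whenever rho is below about 0.5. The documents do not support this. Sample size does not identify 2.2 as the SD of scores, and parts of its wording lean towards change, since the target is framed as a decrease of two symptoms. No rho is given. Which SD was meant, and what correlation was assumed, are details a condensed article may leave to a fuller plan. Even on the single-time reading, a threshold near 0.5 belongs to 32 complete pairs per arm. With 50 enrolled and all baselines kept it is near 0.38. The entry criterion of at least three symptoms would tend to lower rho, but that does not supply a value.

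A reader might also take the complete-data ratio at rho 0.5 (0.75, equal to 33% more participants) as the gain here. That is too large, because the planned model already draws some information from the baselines of participants who drop out.

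Finally, a model with baseline YFAS as a covariate may look interchangeable with the common-baseline model. It removes the same excess variance from the 3-month contrast, but participants with a baseline only supply no outcome row and leave the analysis, contrary to the stated intention to keep baseline scores.

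**Conclusion.** The point holds as one of efficiency. As specified, the primary model yields a difference in change that is valid and unbiased, but less precise than a common-baseline contrast for every rho below 1 when the SDs are equal. In the planned design the variance ratio is about 0.73, 0.81 and 0.89 at assumed rho of 0.3, 0.5 and 0.7. This rests on 30% dropout, equal SDs at baseline and 3 months, and reading the reported effect as the between-arm interaction contrast. The same inefficiency applies to the secondary outcomes given the same model, with a size that depends on each outcome's own correlation.

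A power shortfall is not shown. It is possible only if 2.2 is the SD of single-time scores and rho is below about 0.38 as enrolled, or below about 0.49 at the stated 32 per arm.

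**What to change.** Constrain the three arms to one common baseline mean. Drop the group main effect at baseline, and keep time, the group-by-time terms at 3 and 6 months, and the unstructured covariance. That leaves seven means (one baseline, six follow-up) in place of nine. Name the primary effect as the between-arm difference at 3 months with its confidence interval. Use the same structure for the dietary, depression, anxiety and stress models. The unconstrained fit can stay as a sensitivity check.

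Baseline-only participants remain in the likelihood, as the section intends, which is the reason to prefer this to a baseline-covariate model. It would also help to state whether 2.2 is the SD of scores or of change.

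The cost is a line of model specification and a recorded amendment before any unblinded analysis. No new data are needed.
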